## Abstract

**Background:**

Multimorbidity (co-occurrence of ≥2 chronic conditions) in older adults is a global health challenge, often managed with polypharmacy that carries risks of adverse events and drug–drug interactions. As a pilot randomized controlled trial (RCT), this study first aims to assess the feasibility of low-frequency transcutaneous electrical nerve stimulation (Lo-TENS) delivery in older adults with multimorbidity and estimate effect sizes for a subsequent definitive trial. Second, we examine the efficacy of Lo-TENS as an adjunct to routine clinical management for improving blood pressure, glycemic control, and lipid profiles, and explore the underlying autonomic nervous system (ANS) modulation mechanisms through analysis of heart rate variability and key inflammatory/metabolic biomarkers, which are hypothesized to mediate Lo-TENS’s beneficial effects on clinical indicators.

**Methods:**

A pilot single-center, single-blinded, sham-controlled RCT will enroll 50 older adults (≥60 years) with multimorbidity (≥2 of EH, T2DM, hyperlipidemia). Participants will be randomly allocated (1,1) to receive Lo-TENS (2 Hz, 30 min/day, 5 days/week for 4 weeks) plus routine care or sham Lo-TENS plus routine care. Co-primary outcomes are office systolic blood pressure (SBP), fasting blood glucose (FBG), and low-density lipoprotein cholesterol (LDL-C) at post-intervention. Secondary outcomes include 24-h ambulatory BP, heart rate variability (HRV), inflammatory/metabolic biomarkers, and quality of life. Mechanistic analyses will explore mediation by ANS and inflammatory markers. Follow-up assessments will be conducted 4 weeks post-intervention.

**Discussion:**

This trial will provide evidence on the effectiveness of Lo-TENS on clinical outcomes in multimorbidity in older adults, and explore the underlying mechanisms through which Lo-TENS may alleviate the clinical indicators of multimorbidity, specifically by analyzing heart rate variability and key inflammatory and metabolic biomarkers.

**Trial registration:**

www.chictr.org.cn, identifier ChiCTR2400093956.

## Introduction

1

Multimorbidity, defined as the co-occurrence of two or more chronic conditions in a single individual, affects over 60% of adults aged ≥60 years globally and is associated with increased mortality, reduced quality of life, and high healthcare costs (1, 2). Common multimorbidity combinations in older adults include essential hypertension (EH), type 2 diabetes mellitus (T2DM), and hyperlipidemia—conditions that share overlapping pathophysiological pathways and often require polypharmacy for management (3). While polypharmacy is a cornerstone of multimorbidity care, it carries significant risks in older adults, including drug–drug interactions, adverse drug events, and reduced treatment adherence (4, 5), highlighting an urgent need for safe, non-pharmacological adjunctive therapies (6, 7).

Sympathetic over-activation has emerged as a unifying pathophysiological driver of EH, T2DM, and hyperlipidemia, particularly in older adults (8, 9). Age-related declines in autonomic nervous system (ANS) regulation lead to increased sympathetic tone, which exacerbates vascular dysfunction (contributing to EH), impairs insulin sensitivity (worsening T2DM), and promotes pro-inflammatory responses (driving hyperlipidemia) (10, 11). In older adults with multimorbidity, sympathetic over-activation exerts synergistic adverse effects across cardiovascular and metabolic systems: increased catecholamine release elevates vascular tone (EH) and impairs insulin sensitivity (T2DM), while sympathetic-driven pro-inflammatory responses exacerbate lipid dysregulation (hyperlipidemia) (12). This unifying pathophysiology creates a unique therapeutic target—ANS modulation—for a single adjunctive intervention to improve multiple co-existing conditions simultaneously (13).

However, no pilot randomized controlled trial (RCT) has yet investigated Lo-TENS for common multimorbidity in older adults, nor explored its mechanistic pathways through ANS and inflammatory/metabolic biomarkers. Low-frequency transcutaneous electrical nerve stimulation (Lo-TENS; ≤10 Hz) is a non-invasive, low-risk intervention that modulates ANS activity by stimulating peripheral nerves (14). Prior studies have shown that Lo-TENS reduces sympathetic tone (measured via plasma norepinephrine levels and HRV) and improves clinical outcomes in patients with single chronic conditions, such as EH and T2DM (15–17) For example, Stein et al. demonstrated that 2 Hz Lo-TENS robustly reduces sympathetic activity and increases parasympathetic tone in healthy adults (15), and subsequent studies have validated these effects in older adults with cardiovascular conditions (18, 19). A recent randomized trial in patients with type 2 diabetes further suggested that TENS may improve glycemic variability, although its effect on HbA1c remains inconclusive, warranting further mechanistic investigation (20).

A pilot RCT is critical for this research question to assess feasibility (e.g., recruitment, intervention adherence, attrition) and estimate effect sizes for a subsequent definitive trial (21). As an pilot RCT, this study first aims to assess the feasibility of Lo-TENS delivery in older adults with multimorbidity and estimate effect sizes for a subsequent definitive trial. Second, we examine the efficacy of Lo-TENS as an adjunct to routine clinical management for improving blood pressure, glycemic control, and lipid profiles in older adults with common multimorbidity (≥2 of EH, T2DM, hyperlipidemia). Third, we explore the underlying mechanisms of Lo-TENS by testing whether changes in ANS function (HRV, norepinephrine) and inflammatory/metabolic biomarkers (IL-6, adiponectin, FGF21) mediate its effects on clinical outcomes (22, 23).

## Methods

2

### Study design

2.1

This is a single-center, single-blinded, sham-controlled pilot RCT conducted at The Second People’s Hospital of Kunming (Kunming, China). The study adheres to the SPIRIT (Standard Protocol Items: Recommendations for Interventional Trials) guidelines (24) and TIDieR (Template for Intervention Description and Replication) checklist (25) (see Table 1). Participants will be randomly allocated to either the Lo-TENS group or the sham Lo-TENS group in a 1:1 ratio. The intervention period is 4 weeks, with follow-up assessments conducted 4 weeks post-intervention (total study duration: 8 weeks per participant). The study flowchart is presented in Figure 1.

**Table 1 tab1:** The intervention protocol for each group base on the TIDieR template.

Item	1. Lo-TENS plus routine clinical management group	2. Sham stimulation plus routine clinical management group
1. Why	The stimulation protocol is adopted from previous studies. A self-adhesive electrode plate is affixed to the dorsal aspect of the first and second metacarpal bones, an additional electrode plate is positioned over the muscle belly of the proximal radius, with both upper limbs receiving the same placement (Figure 2). Therefore, the same protocol was adopted in our trial. The routine clinical management is to ensure participants’ multimorbidity is stable.	The sham stimulation group served as an active control group, enabling us to determine whether the observed changes in the stimulation groups are a function of maturation, repeated testing, or placebo effect.
2. What materials	KD-2A, Yaoyang Kangda Electronic Instrument Co., Ltd., Beijing, China. 5 × 5 cm self-adhesive electrodes.	KD-2A, Yaoyang Kangda Electronic Instrument Co., Ltd., Beijing, China. 5 × 5 cm self-adhesive electrodes.
3. Procedures	Participants will be sitting in a comfortable chair. After cleaning the skin, Lo-TENS therapy will be performed. One channel to one upper limb, and both upper limbs will be placed.	The placement of electrodes is the same as in group 1.
4. Who provided	Experienced physiotherapists	Experienced physiotherapists
5. How	The stimulation parameters are set as follows: mode, continuous; waveform, bidirectional asymmetric square wave; pulse width, 200 μs; frequency, 2 Hz. The stimulation intensity in milliamps (mA) will be tailored to the individual’s sensation, permitting slight muscle contraction but ensuring that pain or any discomfort is avoided.	Except there will be no actual treatment, the other setting will be the same as in group 1.
6. Where	The therapy will be performed in the physiotherapy room of the hospitals.	The therapy will be performed in another physiotherapy room of the hospitals.
7. When and how much	Participants in this group will undergo their stimulation in one 30-min session per day, over a period of 5 days per week, for a total of 4 consecutive weeks (resulting in 20 sessions in total).	Except there will be no actual treatment, the others will be the same as in group 1.
8. Tailoring	The stimulating intensity will be tailored to the participant’s tolerance, but without any pain or discomfort.	As no electrical current is delivered, individualized adjustment of stimulation intensity is not applicable. However, participants may adjust their posture to ensure comfort.
9. How well	Intervention adherence will be quantified as the percentage of completed sessions (≥80% adherence defined as successful); assessors are blinded to group allocation to ensure objective outcome measurement.	Same as Lo-TENS group; adherence is quantified as session completion, and assessor blinding is maintained for objective outcome measurement.

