#### Recruitment and informed consent

2.2.2

Participants will be recruited from the outpatient department and community health centers of The Second People’s Hospital of Kunming between December 2025 and May 2027. Recruitment strategies include poster advertisements, physician referrals, and community health education sessions. Eligible participants will be invited to attend a pre-recruitment briefing, where study staff will explain the study purpose, procedures, risks, and benefits. Those who agree to participate will sign a written informed consent form (approved by the hospital’s Ethics Committee) prior to any study-related procedures. Informed consent will be administered by trained rehabilitation therapists to ensure participants fully understand the protocol.

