#### Blinding

2.3.3

The study is single-blinded: participants are blinded to group allocation, but therapists (who deliver the intervention) cannot be blinded due to the need to adjust TENS intensity. To minimize bias, outcome assessors and data analysts are also blinded to group allocation. A post-intervention blinding effectiveness survey will be administered to all participants (a 5-point Likert scale: 1 = certain sham, 2 = likely sham, 3 = unsure, 4 = likely real, 5 = certain real). The proportion of participants who correctly guess their group allocation will be calculated to quantify unblinding bias, and results will be reported in the trial’s primary analysis.

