### Data collection and management

2.7

Data are collected by trained research assistants (blinded to group allocation) at baseline, post-intervention, and 4-week follow-up. Clinical data (BP, FBG, LDL-C) are recorded directly into a secure electronic database (EpiData 3.1). Blood samples are stored at −80 °C until batch analysis to ensure consistency. Dual independent data entry is performed to minimize errors; discrepancies are resolved by a third researcher. All data are anonymized (identified by participant ID only) and stored in a password-protected server at The Second People’s Hospital of Kunming. Data access is restricted to the study team, with the corresponding author responsible for data sharing (per reasonable requests from other researchers).

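### Each arm has its own treatment room, so any setting effect is fully confounded with stimulation

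*Protocol article*

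**What the plan says.** Table 1 (the TIDieR table in section 2.1), item 6, places the two arms apart. For Lo-TENS: "The therapy will be performed in the physiotherapy room of the hospitals". For sham: "The therapy will be performed in another physiotherapy room of the hospitals". No reason is given, and no rotation or sharing of rooms is described.

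Item 4 has the same entry in both columns, "Experienced physiotherapists", and does not assign therapists to a room or an arm. Item 1 gives the purpose of the sham arm as "enabling us to determine whether the observed changes in the stimulation groups are a function of maturation, repeated testing, or placebo effect". Section 2.3.2 matches device, electrode placement, seated time, calibration and electrode checks between arms.

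On blinding, section 2.3.3 says participants are blinded, "but therapists (who deliver the intervention) cannot be blinded due to the need to adjust TENS intensity", and that "outcome assessors and data analysts are also blinded to group allocation". Section 2.7 adds: "Data are collected by trained research assistants (blinded to group allocation) at baseline, post-intervention, and 4-week follow-up". The only check on blinding is a survey of participants. The article does not say where outcomes are assessed.

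**The concern.** A sham-controlled design aims for arms that differ only in the current delivered. Item 6 adds a second systematic difference. Whatever differs between the rooms (noise, temperature, privacy, who is present) differs between the arms throughout treatment.

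Office SBP is a co-primary outcome, and HF-HRV and norepinephrine are both outcomes and candidate mediators. These are the measures on which setting and attention could plausibly act. Estimating effect sizes for a definitive trial is part of the first stated aim, so a room effect would be carried into the planning of that trial.

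There is also a secondary risk. A fixed room per arm is a marker of allocation for anyone who learns which room is which. Blinded assessment is the article's stated answer to unblinded therapists (sections 2.3.3 and 3.4), so a marker that could reach assessors deserves attention.

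**Working it through.** The plan states no figure on this point. The check is a reading of the text, followed by illustrations whose inputs are marked as assumptions.

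**1. What is estimable.** Let τ be the effect of stimulation, and let r₁ and r₂ be the effects of the Lo-TENS room and the sham room on an outcome. Under item 6:

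- expected difference, Lo-TENS minus sham = τ + (r₁ − r₂)

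The room indicator and the arm indicator are the same variable, so a model containing both cannot be fitted. Baseline measurement does not help. It precedes treatment, so a room effect that arises during treatment appears in the group × time interaction, which is the term section 2.8 tests.

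If each arm spends half its sessions in each room, and session effects average, both arms carry (r₁ + r₂)/2 and the expected difference is τ.

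**2. Size of the shift (assumption).** The article gives no room effect. For an assumed r₁ − r₂ in SBP of 0, 2, 3 or 5 mmHg, the treatment estimate shifts by 0, 2, 3 or 5 mmHg.

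**3. False-positive rate (assumption).** Treat the room effect as random, with intraclass correlation ICC, one room per arm and n participants per arm, in a simple two-group comparison that ignores room:

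- inflation of the standard error = √(1 + n·ICC/(1 − ICC))
- actual error rate = 2·(1 − Φ(z/inflation))

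Inputs are n = 25 (section 2.5) and the Bonferroni level 0.0167 (section 2.8), for which z = 2.393. Worked for ICC = 0.02: 25 × 0.02/0.98 = 0.510; √1.510 = 1.229; 2.393/1.229 = 1.947; error rate about 0.05.

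| Assumed ICC | Inflation | Nominal 0.0167 becomes | Nominal 0.05 becomes |
|---|---|---|---|
| 0 | 1.000 | 0.017 | 0.05 |
| 0.01 | 1.119 | 0.03 | 0.08 |
| 0.02 | 1.229 | 0.05 | 0.11 |
| 0.05 | 1.522 | 0.12 | 0.20 |

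These show sensitivity only. Nothing in the article says which row applies, and at ICC = 0 there is no inflation.

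**4. Is a rota practicable?** Inputs are 50 participants (section 2.5), 20 sessions of 30 minutes (Table 1, item 7), and recruitment "between December 2025 and May 2027" (section 2.2.2), which is 18 months or about 391 weekdays.

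- Session time: 50 × 20 × 0.5 h = 500 h
- Load if enrolment is even: 500/391 = 1.28 h per weekday
- Participants in treatment at once: 50/18 = 2.78 per month; 2.78 × 28/30.4 = 2.6

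Swapping two rooms on alternate weekdays gives a participant who attends all 20 sessions on consecutive weekdays 10 sessions in each room.

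**The case against.** The strongest reply is that separate rooms protect participant blinding. Active stimulation allows slight muscle contraction, whereas the sham device is switched off after 10 s, so participants treated side by side could compare what they see and feel. The article does not give this as its reason, but it is a sensible one. It supports keeping the arms apart at any one time. It does not require the same room for the same arm throughout.

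A reader might infer three stronger points that the text does not support.

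- **Therapist effects are fully mixed with treatment.** Item 4 describes the therapists identically for both arms and ties none to a room. Therapist confounding is possible, but it is not stated.
- **The room reveals allocation to blinded staff.** An assessor would have to see or be told the room and also know which room is active. The article says neither, and it describes the data collectors separately from the therapists. Analysts would learn the room only if it were recorded. This is a risk and not an established breach.
- **The sham control is defeated.** With device, placement, seated time and number of sessions matched, the sham still controls for maturation, repeated testing and expectation. What is left uncontrolled is a setting effect.

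It also stands that FBG and LDL-C are laboratory assays, that office SBP is the mean of three electronic readings after rest, and that nothing places those readings in the treatment room. A setting effect would have to outlast the session. The feasibility figure assumes even enrolment, and room availability is not given.

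**Conclusion.** The point holds in limited form. Item 6 makes room and arm coincide for every participant, nothing elsewhere in the article corrects this, and no later analysis can undo it. Any setting effect would enter the treatment estimate one-for-one. Its size is unknown and may be zero; the 0 to 5 mmHg range for SBP and the ICC values are assumptions. Exposure is greatest for office SBP, HRV and norepinephrine, and smaller for FBG and LDL-C. Confounding by therapist and disclosure through the room are possibilities that the article leaves open. The change is worth making before enrolment because it removes a bias that cannot be measured afterwards, at little cost.

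**What to change.** Change Table 1, item 6 so that both arms use the same rooms, in one of two ways:

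- swap the two rooms between arms on alternate treatment days, so that the arms remain apart at any one time; or
- use one room with individual, non-overlapping appointments.

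State in item 4 that the same therapists treat both arms. It would help to log room and therapist for each session, in a record kept from blinded staff, so that balance can be checked.

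The cost is a change of wording and an appointment rota. Swapping uses the two rooms already planned. The single-room option needs about 1.3 h per weekday on average, more when enrolment bunches, and depends on room availability. Someone who knows the rota could still infer arm from room on a given day, so the rota should not be shared with assessors. Stimulation settings, sample size and analysis are unaffected.

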**Figure 1 fig1:**
[figure not shown]
Study flowchart of trial process.

### Participants

2.2

#### Eligibility criteria

2.2.1

Inclusion criteria: (1) Aged ≥60 years; (2) Diagnosis of multimorbidity, defined as co-occurrence of ≥2 of the following: EH (diagnosed per Chinese Guidelines for the Management of Hypertension (26)), T2DM (diagnosed per American Diabetes Association guidelines (27)), hyperlipidemia (diagnosed per Chinese Guidelines for the Management of Dyslipidemia in Adults (28)); (3) Medically stable, defined as no acute exacerbation of EH, T2DM, or hyperlipidemia in the past 3 months and no hospitalizations for cardiovascular/metabolic events (e.g., myocardial infarction, stroke, diabetic ketoacidosis) in the past 6 months; (4) Able to understand and comply with the intervention protocol (e.g., attend 4 weeks of TENS sessions); (5) Voluntary participation and signed informed consent.

Exclusion criteria: (1) Contraindications to TENS (e.g., pacemaker/implantable cardioverter-defibrillator, skin lesions at electrode sites, pregnancy); (2) Severe cognitive impairment (Mini-Mental State Examination score <24); (3) Severe comorbidities (e.g., end-stage renal disease, malignant tumors); (4) Use of other non-pharmacological interventions for cardiovascular/metabolic conditions (e.g., acupuncture, massage) within the past 1 month; (5) Unstable medication regimens for EH/T2DM/hyperlipidemia (e.g., dose changes within the past 2 months).

#### Recruitment and informed consent

2.2.2

Participants will be recruited from the outpatient department and community health centers of The Second People’s Hospital of Kunming between December 2025 and May 2027. Recruitment strategies include poster advertisements, physician referrals, and community health education sessions. Eligible participants will be invited to attend a pre-recruitment briefing, where study staff will explain the study purpose, procedures, risks, and benefits. Those who agree to participate will sign a written informed consent form (approved by the hospital’s Ethics Committee) prior to any study-related procedures. Informed consent will be administered by trained rehabilitation therapists to ensure participants fully understand the protocol.

### Interventions

2.3

#### Lo-TENS group

2.3.1

Participants in the Lo-TENS group will receive Lo-TENS plus routine clinical care. Routine care includes standard pharmacological treatment (antihypertensives, antidiabetics, lipid-lowering drugs) and lifestyle advice (diet, exercise) per clinical guidelines, with no changes to medication regimens during the study period.

Lo-TENS will be delivered using a KD-2A TENS device (Beijing Yaoyang Kangda Medical Equipment Co., Ltd., China) with disposable self-adhesive electrodes (5 cm × 7 cm). A 2 Hz frequency was selected based on Stein et al., which demonstrated the most robust reduction in sympathetic activity and increase in parasympathetic tone in healthy adults (7); this frequency has also been validated in prior Lo-TENS studies for cardiovascular/metabolic conditions and is well-tolerated in older adults due to minimal muscle contraction (8, 9). Electrode placement on the dorsal metacarpal bones (1st/2nd) and proximal radius muscle belly targets the median/radial nerves (Figure 2), which project to the spinal cord and brainstem regions regulating ANS activity; this placement avoids fragile skin on the trunk/limb extremities (common in older adults) and is easily accessible for clinical delivery (29). The stimulation parameters are: frequency = 2 Hz, pulse width = 200 μs, intensity = 2–5 mA (adjusted to the participant’s maximum tolerable level without pain). Each session lasts 30 min, 5 days per week, for 4 weeks (total 20 sessions).

**Figure 2 fig2:**
[figure not shown]
The placement of electrodes.

The KD-2A Lo-TENS device will be calibrated weekly by a certified biomedical engineer to ensure consistent stimulation parameters (frequency, pulse width, intensity); all devices will be checked for electrode conductivity prior to each session, and defective electrodes will be replaced immediately.

